# The CHARTER-Ireland trial: can nebulised heparin reduce acute lung injury in patients with SARS-CoV-2 requiring advanced respiratory support in Ireland: a study protocol and statistical analysis plan for a randomised control trial

**DOI:** 10.1186/s13063-022-06518-z

**Published:** 2022-09-14

**Keywords:** COVID-19, CHARTER, Acute respiratory distress syndrome, SARS-CoV-2, Respiratory support, Nebulised heparin

## Abstract

**Background:**

COVID-19 pneumonia is associated with the development of acute respiratory distress syndrome (ARDS) displaying some typical histological features. These include diffuse alveolar damage with extensive pulmonary coagulation activation. This results in fibrin deposition in the microvasculature, leading to the formation of hyaline membranes in the air sacs. Well-conducted clinical trials have found that nebulised heparin limits pulmonary fibrin deposition, attenuates progression of ARDS, hastens recovery and is safe in non-COVID ARDS. Unfractionated heparin also inactivates the SARS-CoV-2 virus and prevents entry into mammalian cells. Nebulisation of heparin may therefore limit fibrin-mediated lung injury and inhibit pulmonary infection by SARS-CoV-2. Based on these findings, we designed the CHARTER-Ireland Study, a phase 1b/2a randomised controlled study of nebulised heparin in patients requiring advanced respiratory support for COVID-19 pneumonia.

**Methods:**

This is a multi-centre, phase 1b/IIa, randomised, parallel-group, open-label study. The study will randomise 40 SARs-CoV-2-positive patients receiving advanced respiratory support in a critical care area. Randomisation will be via 1:1 allocation to usual care plus nebulised unfractionated heparin 6 hourly to day 10 while receiving advanced respiratory support or usual care only. The study aims to evaluate whether unfractionated heparin will decrease the procoagulant response associated with ARDS up to day 10. The study will also assess safety and tolerability of nebulised heparin as defined by number of severe adverse events; oxygen index and respiratory oxygenation index of intubated and unintubated, respectively; ventilatory ratio; and plasma concentration of interleukin (IL)-1β, IL6, IL-8, IL-10 and soluble tumour necrosis factor receptor 1, C-reactive protein, procalcitonin, ferritin, fibrinogen and lactate dehydrogenase as well as the ratios of IL-1β/IL-10 and IL-6/IL-10. These parameters will be assessed on days 1, 3, 5 and 10; time to separation from advanced respiratory support, time to discharge from the intensive care unit and number tracheostomised to day 28; and survival to days 28 and 60 and to hospital discharge, censored at day 60. Some clinical outcome data from our study will be included in the international meta-trials, CHARTER and INHALE-HEP.

**Discussion:**

This trial aims to provide evidence of potential therapeutic benefit while establishing safety of nebulised heparin in the management of ARDS associated with SARs-CoV-2 infection.

**Trial registration:**

ClinicalTrials.govNCT04511923. Registered on 13 August 2020.

Protocol version 8, 22/12/2021

Protocol identifier: NUIG-2020-003

EudraCT registration number: 2020-003349-12 9 October 2020

**Supplementary Information:**

The online version contains supplementary material available at 10.1186/s13063-022-06518-z.

## Administrative information

‘Note: the numbers in curly brackets in this protocol refer to SPIRIT checklist item numbers. The order of the items has been modified to group similar items (see http://www.equator-network.org/reporting-guidelines/spirit-2013-statement-defining-standard-protocol-items-for-clinical-trials).’

## Introduction

### Background and rationale {6a}

SARS-CoV-2 generates a robust immune response, with inflammatory cytokine generation and excessive coagulation activation [1]. Excess coagulation leads to increased fibrin formation, resulting in deposition of hyaline membranes in the alveolar spaces and microvascular thrombi, contributing to the development of ARDS and multiorgan failure [1, 2]. A rise in d-dimer level associated with the extent of fibrin formation correlates well with the severity of ARDS [1]. Lan et al. showed in their meta-analysis that nebulised heparin can be of benefit in burn injury to the lung, a condition associated with procoagulant and inflammatory effects also [3]. Further laboratory research by Camprubí-Rimblas et al. examined the in vitro effects of heparin on a cellular model of ARDS, showing a reduction in pro-inflammatory markers in heparin-treated cells [4].

There is scientific rationale for the use of nebulised heparin in the treatment of SARS-CoV-2 also [5]. Dixon et al. found secondary outcome evidence of benefit through reduction in the Murray Lung Injury Score and reduction in the development of ARDS along with improving outcomes at day 60 in mechanically ventilated patients at risk of developing ARDS who received nebulised heparin. However, the primary outcome of improvement in physical function score and mortality were not different [6]. This study gives further indication that nebulised heparin may limit fibrin deposition and could help to prevent progression of ARDS [6]. Furthermore, SARS-CoV-2 spike glycoprotein has been found to bind heparin, causing a conformational change which prevents the virus from entering the cell [7].

This is a preliminary efficacy and safety study, as such d-dimer level is being used as an intermediate marker of efficacy. Higher d-dimer levels are correlated with more severe ARDS in SARS-CoV-2 infection [8]. Lower mean d-dimer levels were found in survivors of SARS-CoV-2 vs non-survivors [9]. This study aims to test the hypothesis that nebulised heparin will cause a reduction in pulmonary microvascular thrombosis, using a reduction in d-dimer as a surrogate marker. Recent studies using nebulised heparin have not shown an increased rate of adverse outcomes when compared with placebo, and this study aims to confirm these findings [6, 10].

A number of previous clinical trials in patients with, or at risk for, ARDS or with related conditions, report that nebulised heparin is safe, and may have therapeutic potential, limiting pulmonary fibrin deposition, reducing acute lung injury progression and facilitating recovery. Furthermore, the potential exists for heparin to directly inactivate SARS-CoV-2. Given these findings, we believe that a safety and feasibility study of nebulised heparin therapy for the treatment of COVID-19 is warranted.

### Objectives {7}

Our hypothesis is that nebulised heparin will decrease severity of lung injury in SARS-CoV-2 through multiple mechanisms as shown above, and this will be shown through a decrease in procoagulant markers such as d-dimer.

The objective of this safety and feasibility study is to determine if treatment with nebulised heparin, compared to standard care, reduces the severity of the procoagulant response in intensive care unit (ICU) patients with SARS-CoV-2 requiring advanced respiratory support and to assess the safety of nebulised heparin in patients with COVID-19-induced severe respiratory failure.

### Trial design {8}

This is an investigator-led prospective, phase 1b/IIa, multi-centre, randomised, parallel-group, open-label proof-of-principle, superiority study. The study will recruit 40 adult patients infected with SARS-CoV-2 who require advanced respiratory support across multiple centres in Ireland. Randomisation will use a 1:1 allocation to usual care only or usual care plus nebulised unfractionated heparin 6 hourly to day 10 while receiving advanced respiratory support. The study is designed to evaluate whether nebulised unfractionated heparin will decrease the procoagulant state related to ARDS. The study will measure safety outcomes for the administration of heparin via the Aerogen solo nebuliser as a co-primary endpoint and will assess clinical outcomes as secondary endpoints. The study adheres to the SPIRIT guidance on clinical trials [11].

## Methods: participants, interventions and outcomes

### Study setting {9}

Three intensive care units across Ireland were selected as enrolment sites. The size of the intensive care units differed across the 3 hospitals. However, all ICUs adhere to the JFICM/ICSI intensive care guidelines of 1:1 nurse care in level 3 beds, 1:2 nurse care in level 2 beds, 1 nonconsultant hospital doctor per 6–8 patients and a dedicated consultant physician responsible for the care of the patients in the level 2/3 beds.

### Eligibility criteria {10}

Patients with confirmed SARS-CoV-2 infection receiving advanced respiratory support in an intensive care environment. See Table 1.

**Table 1 Tab1:** Eligibility criteria for participants

Inclusion criteria	Exclusion criteria
Confirmed or suspected COVID-19 If ‘suspected’, results must be pending or testing intended	Enrolled in another clinical trial that is unapproved for co-enrolment
Ability to obtain informed consent/assent to participate in study	Heparin allergy or heparin-induced thrombocytopenia
Age 18 years or older	APTT > 100 s
Requiring high-flow nasal oxygen (>30l/min) or positive pressure ventilator support or invasive mechanical ventilation in the ICU for a time period of no greater than 48 h	Pulmonary bleeding, which is frank bleeding in the trachea, bronchi or lungs with repeated haemoptysis or requiring repeated suctioning
D-dimers > 200 ng/ml	Platelet count < 50 × 10^9^ per l
Acute opacities on chest imaging affecting at least one lung quadrant. ‘Acute opacities’ do not include effusions, lobar/lung collapse or nodules	Uncontrolled bleeding
Currently in a higher level of care area designated for inpatient care of patients where therapies including non-positive pressure ventilatory support (e.g. high-flow nasal oxygen) can be provided	Pregnant or suspected pregnancy (urine or serum HCG will be recorded)
	Receiving or about to commence ECMO or HFOV
	Myopathy, spinal cord injury or nerve injury or disease with a likely prolonged incapacity to breathe independently, e.g. Guillain-Barre syndrome
	Usually receives home oxygen
	Fully dependent on others for personal care due to physical or cognitive decline prior to this illness (premorbid status)
	Death is imminent or inevitable within 24 h
	The clinical team would not be able to set up the study nebuliser and ventilator circuit as required including with active humidification
	Clinician objection
	The use or anticipated use of nebulised tobramycin during this clinical episode
	Any other specific contraindication to anticoagulation including prophylactic anticoagulation not otherwise listed here
	Relapse in clinical condition requiring advances respiratory support in patient that had fully weaned from advanced respiratory support
	Receiving any direct/novel oral anticoagulant

### Who will take informed consent? {26a}

Informed consent is taken by an investigating doctor conducted in accordance with the ethical principles outlined in the Declaration of Helsinki. For trial participants who are unable to give consent due to illness severity, informed assent is obtained from next of kin. Due to the pandemic situation, some modifications to the assent process were required and approval was received from the Irish Health Research Consent Declaration Committee to allow phone assent to be obtained when the next of kin was unable to attend the hospital. If or when these patients regain capacity, their informed consent to continue to participate in the study will then be sought, with this consent then superseding the consent declaration and assent.

### Additional consent provisions for collection and use of participant data and biological specimens {26b}

Provisions for consent/assent to use patient data and biological specimens in future ancillary studies is included in our study protocol and has similar approvals in place.

### Interventions

#### Explanation for the choice of comparators {6b}

As a phase 1b/2a study of a new treatment for this disease, the comparator chosen was standard care in our participants.

#### Intervention description {11a}

Participants assigned to ‘nebulised heparin’ will receive 5ml heparin sodium 5000 I.U./ml (25,000 I.U. in 5 ml), manufactured by Pinewood laboratories, Ballymacarbry, Clonmel, Co. Tipperary. This will be administered via the Aerogen solo nebuliser every 6 h from enrolment to day 10, in addition to the standard care required as determined by the treating team. Participants assigned to ‘standard care’ will receive the standard care required as determined by the treating team and will not be treated with nebulised heparin.

#### Criteria for discontinuing or modifying allocated interventions {11b}

Outlined in Table 2.

**Table 2 Tab2:** Indications for withholding and recommencement of nebulised heparin

Nebulised heparin should be withheld if any of the following occurs:	Nebulised heparin should be recommenced if:
More than 10 days have elapsed since randomisation	Having been withheld because the patient was outside the ICU, the patient returns to ICU
The patient is outside of higher-level care setting	Having been withheld because the patient was not receiving advanced respiratory support, advanced respiratory support is reinstituted
The patient is not receiving advanced respiratory support	Having been withheld because the APTT was unacceptably prolonged, the APTT becomes acceptable
The treating physician deems that there is a clinically unacceptable increase in APTT (>100s)	Having been withheld because there was excessive bloodstaining of respiratory secretions, the bloodstaining of the respiratory secretions has resolved
The treating physician deems that there is excessive bloodstaining of respiratory secretions	Having been withheld for suspected HIT, the patient is found not to have this condition
There is pulmonary bleeding, major bleeding or suspected or confirmed HIT	Having been withheld for ECMO, the treatment with ECMO is stopped
The patient is receiving ECMO or HFOV	Having been withheld for HFOV, the treatment with HFOV is stopped

Each participant has the right to withdraw from the trial at any time. Where the participant gives a reason for withdrawal (they are not obliged to provide a reason), the reason for withdrawal will be recorded. Equally, the investigator may decide to withdraw a patient from the study at any time — in this case, the reason for withdrawal will be recorded. If a patient withdraws from the study, they will be encouraged to complete the follow-up aspect of the study. Also, if a patient withdraws from the study due to a safety event, mandatory follow-up of that event until its resolution will occur.

#### Strategies to improve adherence to interventions {11c}

As a phase 1b/2a study, any issues that arise with adherence to intervention will be reported and will be addressed during the study. These may include staffing issues due to the pandemic or any supply or administration issues related to drug and equipment which may arise. In general, we anticipate high levels of adherence as the intervention is provided in the ICU, by ICU staff.

#### Relevant concomitant care permitted or prohibited during the trial {11d}

Patients receiving or anticipated likely to receive nebulised tobramycin are prohibited from enrolling in the trial or must be withdrawn if this therapy is commenced. Patients receiving direct oral anticoagulants are also prohibited from enrolment.

Treatment with any or all of the following therapies *is not* of itself reason to withhold nebulised heparin: deep vein thrombosis prophylaxis with unfractionated heparin or non-heparin anticoagulants, anti-thrombotic medications, protamine, prone positioning and inhaled nitric oxide.

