#### Plans for collection, laboratory evaluation and storage of biological specimens for genetic or molecular analysis in this trial/future use {33}

Blood samples collected for analysis of interleukin and tissue necrosis factor levels will be stored during the study in the recruiting hospital in temperature monitored laboratory refrigerators. Following completion of recruitment and sample collection, samples will be transferred by a specialist biochemical sample transport company to the primary centre (NUIG/UHG) for processing. This approach has been taken as some of the inflammatory cytokine analyses are not standard assays in the laboratory of the recruiting centres. Only the described analyses will be carried out on these samples, with unused portions of these samples destroyed according to standard laboratory SOPs.

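### Starting nebulised tobramycin removes a patient of either arm from the trial, where ECMO or HFOV only pauses heparin, so study samples to day 10 may go untaken

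*Protocol article*

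**What the plan says.** All references are to the protocol article.

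- **Entry.** Table 1 in Eligibility criteria {10} excludes "The use or anticipated use of nebulised tobramycin during this clinical episode". It also excludes "Receiving or about to commence ECMO or HFOV".
- **Tobramycin after randomisation.** Section {11d} (concomitant care) says patients may not enrol "or must be withdrawn if this therapy is commenced". The trial is the only object the sentence names, and no arm is specified. Tobramycin does not appear in Table 2.
- **ECMO or HFOV after randomisation.** Table 2 in section {11b} lists "The patient is receiving ECMO or HFOV" as a reason to withhold heparin. It gives the matching restart condition, "Having been withheld for ECMO, the treatment with ECMO is stopped", and an equivalent one for HFOV.
- **After withdrawal.** Section {11b} says of patients who withdraw that "they will be encouraged to complete the follow-up aspect of the study". Follow-up is obligatory in one case only: "if a patient withdraws from the study due to a safety event, mandatory follow-up of that event until its resolution will occur". Section {18b} describes follow-up as drawn from records and primary care information.
- **Samples.** Outcomes {12} bases the co-primary d-dimer AUC and the secondary marker AUCs on days 1, 3, 5 and 10. Participant timeline {13} gives days 0, 3, 5 and 10. Section {33} says interleukin and TNF samples are stored at the site and processed centrally, because "some of the inflammatory cytokine analyses are not standard assays in the laboratory of the recruiting centres".
- **Analysis.** Section {20c} analyses enrolled patients as randomised unless they ask for their data to be removed, and uses multiple imputation for missing outcome values.

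**The concern.** A rule about a prohibited drug normally acts on study treatment. This one acts on the patient. It also reaches the standard-care arm, where there is no nebulised heparin to stop, so withdrawing the patient protects nobody from an interaction and can only cost data.

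The rule also fits poorly with the rest of the plan. The protocol already has a mechanism for an entry exclusion that arises later, namely withholding heparin under Table 2, and does not use it here. The intention-to-treat rule wants outcomes regardless of compliance, and the planned per-protocol analysis already gives a place to deal with a deviation.

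What is at stake is data collection. It is not membership of the analysis set: a patient withdrawn under {11d} still counts as randomised. But nothing shown requires blood to be drawn to day 10 after withdrawal. A missed d-dimer might be found in routine care, although the documents do not say on which days it would be measured. A missed cytokine sample is unlikely to be found in any record. Daily data and the day 28 and day 60 data come mainly from health records and are less at risk.

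**Working it through.** **1. Like events set side by side**

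| Event | Entry exclusion (Table 1) | If it starts after randomisation | Restart rule | Arm |
|---|---|---|---|---|
| ECMO | yes | heparin withheld (Table 2) | yes | heparin arm only, in effect |
| HFOV | yes | heparin withheld (Table 2) | yes | heparin arm only, in effect |
| Nebulised tobramycin | yes | patient withdrawn ({11d}) | none | not limited |

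The article gives no reason for the different treatment.

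**2. What one withdrawn patient could lose**

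Inputs: the sampling days in {12} (1, 3, 5, 10) and in {13} (0, 3, 5, 10). Assumption, as a worst case: sampling stops at withdrawal, and all later samples would otherwise have been taken.

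Unobserved share of the AUC window = days after the last sample ÷ length of the window.

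First sample on day 1: intervals 2 + 2 + 5 = 9 days.
- Last sample day 3: (2 + 5)/9 = 0.778
- Last sample day 5: 5/9 = 0.556

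First sample on day 0: intervals 3 + 2 + 5 = 10 days.
- Last sample day 3: (2 + 5)/10 = 0.70
- Last sample day 5: 5/10 = 0.50

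Samples lost: 2/4 = 50% after day 3, and 1/4 = 25% after day 5.

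These are shares of the time window, not of the AUC value.

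**3. Which markers are hardest to recover**

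Outcomes {12} lists 10 secondary markers: IL-1β, IL-6, IL-8, IL-10, soluble TNF receptor 1, C-reactive protein, procalcitonin, ferritin, fibrinogen and LDH. The four interleukins and the TNF receptor make 4 + 1 = 5 of 10 that rest on the study-stored samples of {33}. Both planned ratios, IL-1β/IL-10 and IL-6/IL-10, rest on them too. This reads the TNF term in {33} as the soluble receptor listed in {12}.

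**4. How many patients**

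The documents give no rate of tobramycin use, and anticipated use is excluded at entry, so the number should be small. Sample size {14} raises 19 per group to 20, an allowance of 20 − 19 = 1 per arm. One loss per arm is within it. The point does not depend on how the 19 was obtained.

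**The case against.** The best reply is that the harm is inferred. Section {11d} does not say that sampling stops. The article is a summary, and the full protocol, which is not shown, may well require samples after withdrawal. That stands as a limit on certainty. It does not remove the point, because the withdrawal rule itself is stated, is mandatory, and is what a site would follow.

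A second reply is that withdrawal could mean withdrawal from study treatment, since the next paragraph of {11d} concerns reasons not to withhold heparin. That reading is possible but less natural, because the sentence speaks of enrolling in the trial. If two readings are open, the text needs clarifying anyway.

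Third, ECMO started after enrolment is itself a listed outcome, so ECMO patients have to stay in, and the comparison may be unfair. That is right for ECMO. HFOV is not a listed outcome, and it too only pauses heparin.

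Fourth, section {18b} requires participation only while the patient is in ICU, so some late samples could be missed in any case and the avoidable loss may be smaller than shown. This is fair, but a patient starting nebulised tobramycin within ten days is plausibly still in ICU, so it removes little.

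Finally, multiple imputation is planned, serious adverse events are reported for each patient to 90 days after the last dose, and intention to treat is kept. All of this is true, and it is why the point is minor. Imputation still does not replace a sample that could have been drawn.

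**Conclusion.** The concern holds, as a minor point. As written, the tobramycin rule takes a patient of either arm out of the trial for an event that, had it been ECMO or HFOV, would only have paused heparin. Nothing shown secures that patient's remaining samples.

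The consequence is confined to the few patients affected. If sampling stops at withdrawal, each loses 50% to 78% of the AUC window and one or two of four samples, with the last sample taken on day 5 or day 3. The firmer loss is in the five study-stored secondary markers and the two ratios. The co-primary d-dimer is less exposed, because routine values may exist.

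No association with arm, no bias at trial level and no loss of power is claimed. The conclusion assumes that withdrawal means withdrawal from the trial, and that the full protocol does not separately require sampling afterwards.

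**What to change.** In section {11d}, end the first sentence after the bar on enrolment, delete "or must be withdrawn if this therapy is commenced", and put in its place:

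> If nebulised tobramycin is commenced after randomisation, nebulised heparin must be stopped in the heparin arm (see Table 2). Patients in both arms remain in the trial; all scheduled samples to day 10, serious adverse event data and day 28 and day 60 data are collected, and patients are analysed as randomised.

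In the same edit, add a mandatory row to the withholding column of Table 2 for the start of nebulised tobramycin. The clinical leads should set any restart condition; if none is set, heparin is not restarted. The participant's own right to withdraw in {11b} is unchanged.

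The cost is two sentences and one table row. The samples are already scheduled, so there are no extra patients or procedures. The safeguard is kept, because heparin still stops when tobramycin starts. If the change counts as a substantial amendment, section {25} requires prior approval from the competent authority and the ethics committees, and related documents may need updating. If the full protocol already requires sampling after withdrawal, aligning the wording of {11d} and Table 2 with it is enough.
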